##### Sample 4: Intervention kindergartens in multi-site case study

Data collection in sample 4 includes focus groups and structured interviews of participants in the internal project group.

Focus groups will be used to collect data on teachers’ and assistants’ views of the fidelity, reach and acceptability of the professional development curriculum and the move-play-explore pedagogy, contextual barriers and/or facilitators of implementation; staff’s previous experience from participation in research and professional development programs, views on the fit between the aim of MoveEarly compared to local and national kindergarten policies as well as the social dynamics among staff and children. The focus groups will also address how the director and project group has led professional learning community’s participation in the intervention. Interviews will be conducted physically at 3-, 10- and 18-month follow-ups.

Structured interviews will be used to collect data on the internal project group’s views of the fidelity, reach and acceptability of the professional development curriculum and the move-play-explore pedagogy, contextual barriers and/or facilitators of delivery, staff’s previous experience from participation in research and professional development programs, views on the fit between the move-play-explore pedagogy and local and national ECE policies as well as the social dynamics among staff and children. Interviews will be conducted digitally with directors at 3- and 18-month follow-ups.

#### Analysis plan

##### Observations of children and situated practices, interviews and written work

The analysis of data from observations of children and situated practices, interviews and written work submitted by the teachers during the professional development will be inspired by RTA [116] and supported by NVivo (QSR Version 12.6) as a data management tool. Prior to the analyses, interviews and video data (cut into shorter fragments of 10–15 s [110]) will be transcribed such that all qualitative data has a textual form.

In line with the RTA approach [116], the ultimate analytical purpose of the analysis will be to develop a systematic overview of *themes*—“defined by meaning-unity and conceptual coherence” (p. 77). In this analysis the themes will provide a systematic overview over the themes capturing children’s and staff’s actions, experiences, and meanings related to the move-play-explore pedagogy and professional development. This means that the initial codes in the analytical work will be anchored in the trial research questions, the intervention program theory, key findings from the empirical data from the ACTNOW trial, insights from the pilot study and pedagogical content of the intervention (movement-play-exploration). Further, themes will be developed inductively to capture nuances within codes or relevant phenomena that is not connected to a priori code. In the process of searching and reviewing the themes, reflexivity will be highly important. By reflexivity in thematic analysis, Clarke and Braun [116] mean a critical reflection over how disciplinary, theoretical and personal assumptions shape the analytical choices, that as a result delimit knowledge that is produced. As MoveEarly is an interdisciplinary project engaging researchers from different disciplines, research paradigms, and traditions, reflection and transparency regarding the criteria for the final chosen themes of analysis are important not only for the analysis but also for research ethics.

Figure 6 illustrates the process of RTA of the data sets. The main steps distinguished by Clarke and Braun [116], such as familiarisation with the data, developing codes, as well as searching and reflexive revision of the themes, are included. This analytical strategy will lead to the final display of themes embracing the a) children’s experiences with the move-play-explore pedagogy, b) situated practices of movement-play-exploration in kindergartens and c) teachers’ meanings and experiences connected to implementation of the intervention. Elements from grounded theory will be employed to study children’s experiences (a) and situated practices (b), such as comparative approaches and deviant case analysis [215]. The main aim of grounded theory is to provide a systematic means for constructing theories of causation [216]. This approach allows for both inductive and deductive development of concepts by confirming or disproving hypotheses [217]. By using grounded theory, researchers can thoroughly familiarise themselves with and gain a profound understanding of the data. This deep comprehension is facilitated through the process of open coding, which involves researchers identifying common themes from various sources and agents [218]. To study implementation of the intervention (c) we will include testing of context-mechanism-outcome configurations developed prior to initiating the trial [199].

**Fig. 6 Fig6:**
[figure not shown]
Steps in reflexive thematic analysis of qualitative data

##### Children’s drawings

Analyses of children’s drawings will build on the assumption of drawings being “graphic representations” [219] (p. 77) of diverse experiences and events in children’s life [220, 221]. We hypothesize that the move-play-explore pedagogy will have an influence on the content of the children’s drawings. The 5–6-year-old children will be asked to draw: “In kindergarten, what was the most joyful activity you participated in this week?”. The content analysis of the drawings will register both the occurring themes and its frequency [222], which will be compared between intervention and control kindergartens. Each picture will be scanned and marked with group, the child age and gender. Next, the pictures will be scanned and coded in In vivo (Atlas. TI 8.0 software) where specific names will be given to individual elements pictured. These codes will be clustered thematically, and each of the pictures will be secondary coded as *including* or *not including* the identified themes. This dataset will be analysed quantitatively and compared between groups.

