##### Sample 3: Multi-site case study

We will purposively sample 8 intervention kindergartens and 4 control kindergartens to participate in the multi-site case study. Kindergartens will be sampled for diversity in terms of the extent to which the kindergarten seems responsive to the intervention (assessed by baseline questionnaire and initial project description), urban and suburban locations, outside and inside facilities, and the kindergarten’s owner and profile. This approach allows a rich inquiry into intervention implementation in several different, naturalistic settings, and thus allow a more in-depth understanding of the phenomena than a single case can provide [200].

As the intervention relates both to the kindergarten staff and children, both groups will be included in the qualitative studies. In this way, we seek to better understand children’s whole bodily repertoires, and the conditions for them, when children move, play, or explore their environments. Considering children’s tendency in being enactive and easily engaging in activities, showing a genuine interest and enthusiasm (i.e., agency), we will study children’s behaviour as meaningful projects that extend out into the world and are deeply embedded with the environment. We will intertwine in our design both *child perspectives* and *children’s perspectives* as defined by Sommer, Pramling Samuelsson and Hundeide [201]. We understand *child perspectives* as “created by adults who are seeking, deliberately and as realistically as possible, to reconstruct children’s perspectives, for example through scientific concepts concerning children’s understanding of their world and their actions in it” [201] (p. 22). However, although “child perspectives attempt to get as close as possible to children’s experiential world they will always represent adults’ objectification of children” [201] (p. 22). The *children’s perspectives* on the contrary “refer to the perceptions of the non-adult subjects themselves” (p. 22), and capture children’s ‘here and now’ experiences, perceptions, and understandings of their physical and social environments.

A range of methods will be used to capture kindergarten practices, including staff, children’s and child perspectives:

 Staff observation of children

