##### Quantitative data

In sample 1, we will analyse between-group effects on an individual and institutional level. In sample 3, we will analyse between-group effects or main effects of time among intervention kindergartens on an institutional level. Analyses will follow the approaches and procedures outlined in Sect. "Development of measures of movement competence, creativity, playfulness, explorative behaviour and well-being in young children" but will additionally apply Generalized Estimating Equations to model categorical data from questionnaires [223]. Analyses of potential moderators or mediators will be performed as described inSect. "Secondary aims", using both process and outcome evaluation data on the child and kindergarten level.

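### Children's drawings are marked with group before subjective theme coding, with no masking step stated, and the 8 v 4 case-study comparison they feed is not a randomised one

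*Protocol article*

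**What the plan says.** All references are to the protocol article.

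- **Drawings, analysis** (process evaluation analysis plan, Children's drawings). The hypothesis is explicit: "We hypothesize that the move-play-explore pedagogy will have an influence on the content of the children’s drawings". Themes and their frequency are registered, "which will be compared between intervention and control kindergartens". On handling: "Each picture will be scanned and marked with group, the child age and gender". Then: "Next, the pictures will be scanned and coded in In vivo". Elements are named, the names are clustered into themes, and each picture is scored for whether it includes each theme. The section ends: "This dataset will be analysed quantitatively and compared between groups".
- **Source of the drawings** (Sample 3: Multi-site case study). Drawings are a case-study method. "We will purposively sample 8 intervention kindergartens and 4 control kindergartens". The sampling seeks diversity in location, facilities, owner and profile, and in how responsive the kindergarten seems, the last being "assessed by baseline questionnaire and initial project description".
- **Other Sample 3 data** (Quantitative data). "In sample 3, we will analyse between-group effects or main effects of time among intervention kindergartens on an institutional level".
- **Masking** (Timeline, randomization and blinding). As few researchers and assessors as possible are to know the allocation and the hypotheses. Data management and quality control measures adds that the database is locked before the allocation is opened.

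**The concern.** Naming what a child has drawn, deciding which names form a theme and deciding whether a picture contains that theme are all matters of judgement. The themes are also built from the same pictures that are then compared. If the arm is attached to the picture during this work, a coder who knows the hypothesis can lean towards it without intending to. The later quantitative comparison cannot separate that lean from a real effect.

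The set of kindergartens raises a second question. A between-arm difference in a subset keeps the protection of randomisation only if the subset was chosen in the same way in both arms, on information unaffected by allocation. Here one selection criterion draws on a document that exists in one arm only.

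What is at stake is interpretation. The process evaluation serves the second primary research question and is meant to help readers understand the trial's findings. A difference in drawings between arms could be read as evidence that children experienced the pedagogy, when part of it might come from coding or selection.

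**Working it through.** The plan states no figure on this point, so the check is mainly a reading of sections against each other.

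**1. What group means.** Alone, the word could mean a department or child group. The preceding text compares intervention with control kindergartens, and the section closes with a comparison between groups. Trial arm is the natural reading.

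**2. Order of steps.** Marking comes first. Coding is introduced by the word Next, followed by clustering and theme scoring. No step removes or hides the mark. Set beside the masking aim in Timeline, randomization and blinding, the two do not fit: the arm travels with the item being rated.

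**3. When and by whom the project description is written.** Written work, including digital meetings, makes it one of three pieces produced by the project group during the intervention period. Sample 2: Intervention kindergartens lists written work among data collected from intervention kindergartens only. Directors learn their group once child recruitment is complete, and the intervention starts in November 2024. The document therefore postdates allocation and has no control counterpart. Of the two sources named for judging responsiveness, only the baseline questionnaire exists for controls.

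**4. Consequence for the contrast.** The 8 and the 4 are chosen on different information. Since the aim is diversity and not the best responders, the direction of any resulting bias cannot be stated.

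**5. How much a formal test could show, even with masked coding.** Inputs: 8 and 4 kindergartens (Sample 3), 25 and 25 (randomisation section), significance level 0.05 (analysis plan, taken as two-sided). Assumption: equal between-kindergarten SD in both arms, which the article does not give. For a two-sample t-test on kindergarten summaries, df = n1 + n2 − 2 and the noncentrality is d / √(1/n1 + 1/n2), with d in kindergarten-level SDs.

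- 8 v 4: df = 10, √(1/8 + 1/4) = √0.375 = 0.612. The difference detectable with 80% power is d ≈ 1.90. Power is about 11% at d = 0.5, 32% at d = 1.0 and 60% at d = 1.5.
- 6 v 6: detectable d ≈ 1.80.
- 25 v 25: √(1/25 + 1/25) = √0.08 = 0.283. Detectable d ≈ 0.81.

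The small number of kindergartens matters far more than the 2:1 split. There are C(12,4) = 495 ways to split 12 kindergartens 8/4, so a permutation test is possible, but any test here is weak. This supports descriptive reporting. It is not itself the fault.

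**The case against.** **Coders may not see the mark.** The article does not say that they do, and a coding manual could provide masking. This stands in part: visibility is an inference. But the point rests on a stated sequence and not merely on silence, because the article chooses to mark the arm before coding.

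**Purposive sampling is a legitimate qualitative choice.** This stands in full. It serves the question of what works for whom and why, and it should stay. The difficulty is only the between-arm comparison laid on top of it.

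**The plan already places practice comparisons elsewhere.** Samples and methods assigns between-group testing to the research in all kindergartens and describes the case study as ethnographic. Quantitative data sets Sample 3 analysis at institutional level and offers change over time within intervention kindergartens as an alternative to a between-group contrast. This stands, and it narrows the point. For the drawings, however, the between-arm comparison is stated outright.

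**Stronger readings that the article does not support.** A reader might infer that generalized estimating equations will be run on 12 kindergartens, with too many false positives. The article reserves that method for categorical questionnaire data, and none of the methods listed for Sample 3 is a questionnaire. A reader might also infer that promising intervention kindergartens are being picked. The text says the sampling is for diversity in responsiveness. Nor does any section say that the drawings will support the effectiveness claim.

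**Conclusion.** The point holds and is minor. As written, the drawing procedure allows unmasked coding of a subjective measure under a stated hypothesis, contrary to the trial's own masking aim. This rests on reading group as trial arm and on the absence of any masking step between marking and coding. The drawing comparison, and any other Sample 3 between-group contrast, is not a randomised comparison, because one selection criterion uses a post-allocation document found only in the intervention arm. The article gives nothing from which to size the coder bias or to sign the selection bias. The child-outcome analysis of all randomised kindergartens is unaffected.

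**What to change.** 1. **Mask the drawing coders.** Label each drawing with a neutral code that reveals neither arm nor kindergarten. Hold arm in a separate key and merge it only after the theme list and the scoring of every picture are locked. State this in the Children's drawings analysis section. The cost is one re-labelling step. The article appeared on 10 December 2025 and the intervention runs to June 2026, so drawings from the end of the second year can be handled this way. First-year drawings that are marked but not yet coded can be re-labelled. If any have already been coded with the arm visible, report that.
2. **Keep the purposive sampling and change the claim.** Say that the drawing comparison and other Sample 3 between-group contrasts are descriptive, and that the 12 kindergartens were not selected alike in the two arms. The cost is a formal between-group p-value that 8 v 4 kindergartens could support only weakly.
3. **Rest between-group conclusions about practice on Sample 1**, which covers all kindergartens. Its pedagogical practice measure is a self-assessment by staff who know their group, so that limitation should be stated alongside. The contrast does keep the randomised allocation.

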##### Quantitative data

In sample 1, we will analyse between-group effects on an individual and institutional level. In sample 3, we will analyse between-group effects or main effects of time among intervention kindergartens on an institutional level. Analyses will follow the approaches and procedures outlined in Sect. "Development of measures of movement competence, creativity, playfulness, explorative behaviour and well-being in young children" but will additionally apply Generalized Estimating Equations to model categorical data from questionnaires [223]. Analyses of potential moderators or mediators will be performed as described inSect. "Secondary aims", using both process and outcome evaluation data on the child and kindergarten level.

## Privacy protection and ethical perspectives

Our research group has extensive experience with large-scale data collections in children aged 3–6 years. All tests are specifically developed for young children and both physical and app-based measures are based on playful activities, which children generally enjoy. We will arrange all assessments in the kindergarten setting in collaboration with staff to meet each individual child’s needs of a safe environment and support. We acknowledge that assessments could cause stigma to children and families in the margins, children with disabilities, or children who grow up in families with little attention to ‘healthy living’. Efforts will be made to respect all children and families where normality can find many variations.

ECE is a gendered field with an almost entirely female workforce [224]. Regarding PA level and rough-and-tumble play, boys benefit more from the kindergarten setting than girls [20]. Moreover, it has been argued that traditional assessments of motor competence are biased towards skills integral to traditional male sports [225]. We will address these challenges by ensuring that gender perspectives are a key consideration in the development of the pedagogical design, assessment tools, and intervention implementation. We will examine moderation by gender to investigate a potential gender effect. The focus of MoveEarly may appeal to prospective and current male ECE staff, potentially contributing to improving gender equality in the ECE workforce [224].

The project will conform to the ethical guidelines defined by the World Medical Association’s Declaration of Helsinki and its subsequent revisions and has been approved by the Western Norway University of Applied Sciences’ ethics committee (reference number 22/11664–5). The study is conducted in accordance with Western Norway University of Applied Sciences’s internal control system and General Data Protection Regulation (EU 2016/679), approved by the Western Norway University of Applied Sciences’ privacy protection office and registered in the Sikt registry (reference number 186698). We will obtain written informed consent from each participant prior to data collection. We will follow the Vancouver recommendations for authorship policy to maintain high standards in scientific publishing.

## Data management and quality control measures

High quality in data collection, data management, and data analysis is of crucial importance to ensure valid study results and secure privacy protection of participants. Data collectors will be thoroughly trained prior to testing. A standardized protocol including a thorough description, pictures and/or videoclips of all assessments will be developed and used for training. Intertester reliability will be assessed for measures requiring observation. Training also includes a risk and vulnerability analysis as well as an introduction to the data management plan. This plan will ensure that scientific research data generated from the project will be easily discoverable, accessible, verifiable, useable for further research, and interoperable with existing standards. It is mandatory for all researchers who participate in data collection and data management in the MoveEarly project to comply with this protocol manual describing all procedures as approved by Western Norway University of Applied Sciences and documented in our Data Protection Impact Assessment. All non-digital data will be plotted and manually double-checked according to journal sheets and other sources of data, before the research file will be checked for illogical and unexpected values. After the thorough quality control of data, the database will be locked prior to opening the group allocation (18-month follow-up) and prior to performing any statistical analysis of intervention effects.

### Data sharing

The primary investigator and researchers in the MoveEarly project group will have access to the final datasets. The datasets generated in this project may be of interest to researchers, students, clinicians and policymakers within several fields. Sharing and re-use of data facilitate sustainability by increasing knowledge transfer, collaboration and reducing researcher and participant burden. We will obtain consent from participants to share and publish de-identified data to facilitate transparency and re-use of data. Data may be shared with internal and external parties by proposals directed to the primary investigator. As the data will not be anonymous, data will not be made openly available but will be available to researchers on reasonable request under agreed terms and conditions. Information about the project can be found on Western Norway University of Applied Sciences’ web page (https://www.hvl.no/en/research/project/moveearly/) and at ClinicalTrials.gov (https://www.clinicaltrials.gov/study/NCT06488508?cond=NCT06488508&rank=1). All publications related to the project will include contact information and scientific publications will include a DOI number. Table 1 provides metadata for the MoveEarly cluster RCT dataset. Table 1 .

**Table 1 Tab1:** Metadata about the MoveEarly cluster RCT dataset

Key characteristic	Description
Data collection period	01.09.2024–30.06.2026
Timepoints	3 (Sept-Oct 2024, Apr-Jun 2025, Apr-Jun 2026)
Sample	Children aged 4–6 years
Sample size	Approximately 500 children
Type of data	Dataset
Software program	SPSS
Format	.sav
Storage	SILAF (internal secure research server)
Consent	Written informed consent by parent/caregiver
Sharing	A de-identified dataset will be available upon reasonable request
Data on vulnerable groups	Yes, children aged 4–6 years
Classified information	No
Transfer	Sikt Filesender, https://sikt.no/tjenester/filesender
Open repository	Not until the dataset is fully anonymized

